## Methods

### Study Design

This feasibility study and open trial features a single-arm, uncontrolled, within-group design with 3 measurement points at baseline (preintervention), immediately after the intervention (postbaseline), and 3-month follow-up with an embedded qualitative and quantitative assessment. Participants will be allocated to iABCT. The study was registered under Clinicaltrials.gov (NCT03918746) and will be conducted following the extension of the Consolidated Standards of Reporting Trials (CONSORT) statement for pilot and feasibility studies [29], the Consolidated Standards of Reporting Trials of Electronic and Mobile HEalth Applications and onLine TeleHealth guidelines [30], and the Standard Protocol Items: Recommendations for Interventional Trials (SPIRIT) guidelines (Multimedia Appendix 1) [31]. The SPIRIT checklist was used as a guide for reporting this study protocol (version 1; March 6, 2019).

### Eligibility Criteria

The sample will consist of healthy adults from the community. Inclusion criteria are participants should (1) be aged 18 years or older, (2) have adequate knowledge and an understanding of spoken and written Spanish, (3) have a computer with speakers and internet access in a secure setting (home or private office), (4) have an email account, and (5) be able to use a computer and browse the internet. Exclusion criteria are (1) a diagnosis of a mental disorder according to the Diagnostic and Statistical Manual for Mental Health Disorders-Version 5 (DSM-5) [32], (2) alcohol or other substance abuse or dependence, (3) receiving psychiatric or psychological treatment, (4) engaging in ongoing formal meditation training (eg, mindfulness or compassion intervention), (5) presence of heart disease, cardiorespiratory illness, or other severe medical condition, (6) history of epileptic crisis, and (7) unavailability to complete the internet intervention because of surgery or medical intervention.

The study will include participants with and without prior meditation experience. Meditation experience and frequency of meditation will be registered and considered in the data analysis.

### Sample Size

A minimum of 35 participants is considered sufficient to cover the aims of this feasibility study and to provide precise and efficient estimations of parameters (ie, means, standard deviations, effect size, and confidence intervals) for the powering of a larger RCT. Sample estimation is based on the recommended range in the literature (eg, 24 and 50) [33-35] and in line with existing feasibility studies in this field [25,26].

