### Aims and Hypotheses

The main aim of this study is (1) to investigate the feasibility of the Internet Attachment–Based Compassion Therapy (iABCT), a web-based version of ABCT, in the general population. Additional objectives are (2) to analyze the preliminary effects of iABCT on happiness, compassion, self-compassion, dispositional mindfulness, general health, purpose in life, nonattachment, attachment styles, self-criticism, and positive and negative affects at postintervention and 3-month follow-up; (3) to explore cost-effectiveness by means of changes in overall health status levels; (4) to investigate the mechanisms of change, predictors, and associations between outcomes; and (5) to assess adverse or unwanted effects and facilitators and barriers to the intervention received.

The principal hypothesis is that iABCT will be feasible and well accepted by participants in terms of attrition, expectations, satisfaction, usability, and opinion. Second, iABCT will show efficacy in promoting significant changes with moderate-to-large within-group effect sizes in self-reported measures of happiness, compassion, self-compassion, dispositional mindfulness, self-criticizing, nonattachment, purpose in life, attachment, and overall health status. We also hypothesize that gains will be maintained at 3-month follow-ups. Third, changes in overall health levels will demonstrate the cost-effectiveness of iABCT. Fourth, significant associations will be found between changes in compassion, self-compassion, dispositional mindfulness, general health, purpose in life, nonattachment, attachment styles, self-criticism, positive and negative affects, and happiness. Specifically, improvements in happiness scores and overall health status will be predicted by self-reported self-compassion. Increments in secure attachment style would mediate the relationship between self-compassion and happiness. Finally, low rates of adverse or unwanted effects are expected.

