### Statistical Analysis Plan

Normality and homoscedasticity data assumptions will be checked using Kolmogorov-Smirnov (K-S) and Levene tests. Significant differences on categorical variables (eg, sex, educational level, occupation, etc) will be assessed using a chi-square test. Attrition and dropout rates will be calculated by reporting percentages and patterns of missing data. The Little missing completely at random (MCAR) test will be used to assess the assumption that data are MCAR [55]. Means and SDs will be reported for all the measures at each assessment point. A preliminary efficacy analysis will be performed using means of comparison for related samples based on intention-to-treat and per-protocol analyses. Mixed model analyses for primary and secondary outcome measures will be implemented using the linear mixed-effects models (MIXED) procedure with 1 random intercept per subject. *Time* will be treated as a within-group factor, and significant effects will be followed up with pairwise comparisons (adjusted by a Bonferroni correction). Sensitivity analyses will be performed to assess the robustness of the findings in terms of different methods for handling missing data (ie, mixed models with and without imputation, maximum-likelihood estimation, and maximum-likelihood multiple imputation) [56]. Within-group effect sizes (pre vs post and pre vs 3-month follow-up) will be reported using Cohen *d* and its 95% CI. For the analyses of associations between the intervention outcomes, predictors of change, and mechanisms of actions, several statistical tests will be performed such as Pearson correlation, multiple regressions, and mediation analysis using the bootstrapping approach [57]. A cost-effectiveness and cost-utility analysis will be conducted using the GHQ-12 based on literature proposals [58,59]. The mapping technique proposed by Lindkvist and Feldman [59] will be used to predict health state utility values using a crosswalk transformation algorithm from the GHQ-12 to the health utility measure (EuroQoL–5 dimension [EQ-5D]). Spanish tariffs of EQ-5D will be used as the reference population [58,60]. Additionally, participants’ qualitative responses regarding adverse or unwanted effects and facilitators and barriers to the intervention received will be explored using a qualitative content analysis and coding and the categorizing data approach by counting the frequency of words with NVivo software (QSR International). Statistical analyses of quantitative data will be performed using SPSS version 23 for Windows (IBM Corp). The statistical analysis plan (SAP) will be revised by all the study team members before the database is locked for use in the final statistical analysis. Any discrepancies or changes made between the analysis plan in this protocol and final SAP will be explained and reported.

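### The sample size section claims 35 participants give precise estimates, including an effect size, for powering an RCT; the estimates are not precise, and a single-arm within-group d is not the quantity an RCT is powered on

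*Protocol article*

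**What the plan says.** The Sample Size section of the protocol article states: "A minimum of 35 participants is considered sufficient to cover the aims of this feasibility study". It adds that this number serves "to provide precise and efficient estimations of parameters (ie, means, standard deviations, effect size, and confidence intervals) for the powering of a larger RCT". The basis is a rule of thumb: "Sample estimation is based on the recommended range in the literature (eg, 24 and 50", together with the size of earlier feasibility studies in the field. The section uses no target CI width, SD, power or dropout allowance.

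Study Design describes a "single-arm, uncontrolled, within-group design with 3 measurement points". The Statistical Analysis Plan section says: "Within-group effect sizes (pre vs post and pre vs 3-month follow-up) will be reported using Cohen *d* and its 95% CI". It does not say which SD standardises d, and it specifies no other effect size.

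**The concern.** There are two separate problems in one sentence.

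- **Wrong quantity.** A two-arm trial is powered on the difference between arms. A pre-post d from one arm also contains whatever change would have happened without the intervention: time trend, regression to the mean and expectancy. If it is standardised by the SD of change, it also depends on the pre-post correlation. More participants in a single arm would not cure this.
- **Precision.** The text asserts that the estimates will be precise, and the number chosen does not support that.

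What is at stake is the planning of the next trial. A reader who takes the sentence at face value could use the within-group d as the RCT's target difference and treat the SD as well known. The present study's endpoints and analyses are not affected.

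**Working it through.** **The plan's own figure.** The number 35 comes from a quoted range of 24 to 50. There is no formula or input to reproduce; 35 lies inside the range.

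**Inputs**
- n = 35 (Sample Size).
- Within-group d of 0.50 to 1.50, over several outcomes, in the uncontrolled web study of 39 self-critical participants (Introduction, Internet-Delivered Compassion-Based Interventions).
- Between-group d of 0.51 (95% CI 0.30 to 0.63) for satisfaction with life and well-being in the meta-analysis of RCTs (Introduction, Compassion-Based Interventions).
- Dropout of 11.6% in a web-based RCT (same section as the web study).
- Assumed, because the article gives none for the RCT: two-sided 5% level, 80% power, 1:1 allocation, two-sample t test.

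**1. Precision of an SD.** The 95% limits are the estimate times √(34/χ²), with 34 degrees of freedom.
- Lower: √(34/51.97) = 0.81.
- Upper: √(34/19.81) = 1.31.
- Ratio of variances: 51.97/19.81 = 2.6. For a fixed raw difference, RCT size is proportional to the variance, so this is also the range in RCT size from the SD alone.
- One-sided 80% upper limit: √(34/26.94) = 1.12.

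**2. Precision of d.** Take an observed d of 0.50, the lower end of the cited within-group range.
- *Standardised by the change SD.* t = 0.50 × √35 = 2.96. Inverting the noncentral t distribution on 34 degrees of freedom and dividing by √35 gives 0.14 to 0.85.
- *Standardised by the raw SD, pre-post correlation r = 0.7 (assumed).* SE = √[(1/n + d²/2n) × 2(1 − r)] = √[(1/35 + 0.25/70) × 0.6] = 0.139. The interval is 0.50 ± 1.96 × 0.139, or 0.23 to 0.77.
- *Fewer completers.* Applying 11.6% dropout leaves 35 × 0.884 ≈ 31; the change-SD interval becomes 0.12 to 0.87.
- *Top of the cited range.* With n = 50 the change-SD interval is still 0.20 to 0.79.

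**3. Which quantity d is.** Converting a change-SD d to the raw-SD scale multiplies it by √[2(1 − r)]. A value of 0.50 becomes 0.59, 0.50, 0.39 or 0.32 at r = 0.3, 0.5, 0.7 or 0.8. So even before the question of a control group, the unnamed standardiser changes the number.

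**4. What would happen if d were carried forward (illustrative).** Suppose the true between-group d is 0.51, which itself needs 62 per arm.

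| RCT sized on | Per arm | Power at between-group d = 0.51 |
|---|---|---|
| 0.50 (lower end of cited within-group range) | 64 | 82% |
| 1.0 (midpoint of that range, assumed) | 17 | 30% |

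The consequence runs from none to severe, depending on the value observed.

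**5. Attrition.** If 4 of 35 dropped out (11.4%, close to the cited rate, taken as an assumption), the exact Clopper-Pearson 95% CI is 3% to 27%.

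**The case against.** The strongest reply is that the harm to the RCT is not demonstrated. A reader might infer from the within-group range of 0.50 to 1.50, set against 0.51 between groups, that the next trial will be badly undersized. The documents do not support that. The first range covers many outcomes in people selected for harsh self-criticism. The second is for life satisfaction and well-being in clinical and nonclinical samples, and the same meta-analysis gives 0.70 for self-compassion. No value of 1.0 is given for well-being, and sizing on 0.50 leads to no loss of power. Nor does the article say outright that the within-group d will be the RCT's target difference; it lists effect size among the inputs for powering. This reply stands, and the undersizing is therefore shown only as a conditional range.

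It is also fair that the width of the interval for d depends on a standardiser the article leaves open, which is why both versions are given. Both are wide.

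A reader might also object to the hypothesis that "iABCT will show efficacy in promoting significant changes with moderate-to-large within-group effect sizes". That is an editorial matter. The hypothesis names within-group effects, the design is openly declared uncontrolled, and the text elsewhere calls the efficacy preliminary.

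Finally, expected CI widths could sit in a fuller document that is not shown. That would answer a complaint of omission, but not an affirmative claim of precision. No analysis plan can draw a between-group effect from one arm.

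**Conclusion.** The point holds as a fault in the stated justification for the sample size. Effect size is named as an input for powering an RCT, but the design can yield only a within-group d, which does not estimate the difference an RCT needs. The claim of precision also fails: an SD is known to within 0.81 to 1.31 times its estimate, and a d of 0.50 to within roughly ±0.27 (raw SD, assumed correlation 0.7) or ±0.35 (change SD). The SD result assumes approximately normal data and all 35 participants contributing; dropout widens it.

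It would be a mistake to conclude that 35 is too few. It lies within the cited range and is reasonable for feasibility aims. The SD, pre-post correlation, recruitment and attrition are proper planning inputs provided their uncertainty is carried forward. Since the sample size, endpoints and analyses of this study stay as they are, this is something that should be fixed rather than a barrier to the study.

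**What to change.** In the Sample Size section:

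1. Replace the claim of precise and efficient estimation with the expected 95% CI widths at n = 35 and at the expected number of completers. Name the standardiser of d, here and in the Statistical Analysis Plan section, and label any attrition rate as assumed (for example, 4/35 has a 95% CI of 3% to 27%).
2. Remove effect size from the list of inputs for powering the RCT. The within-group d can still be reported as a description of change.
3. State that this study supplies the SD, pre-post correlation, recruitment and attrition, and that the SD will be used with its uncertainty, for example at its one-sided 80% upper limit of about 1.12 times the estimate.
4. State that the RCT's target difference will come from controlled evidence or a minimal important difference.

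The cost is wording only, with no extra participants. The downside is that the stated precision looks less favourable.

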### Recruitment

Recruitment will be conducted online using professional and nonprofessional social media (ie, Facebook, LinkedIn, and Twitter), on the website where the internet intervention will be developed and hosted [36], and through advertisements in local newspapers and radios. The study will also be announced in the Master in Mindfulness program at the University of Zaragoza (Spain) and emailed to lists of contacts interested in meditation issues (eg, students on the master’s program and former students, and people subscribing to the newsletter published by the Mindfulness and Compassion Research Group [37]). In addition, posters will be placed in the following locations: Universitat Jaume I, the University of Valencia, the University of Zaragoza (Teruel, Huesca, and Zaragoza campuses), Miguel Servet Hospital (Zaragoza), and the Arrabal Health Centre (Zaragoza). All participants will access the study voluntarily, and no reimbursement for their participation will be provided in any case. The internet intervention aims to promote psychological well-being but not treat any mental disorders or medical conditions.

People who are interested in the study will be asked to contact the research team, and they will be scheduled for an admission telephone interview to screen for the inclusion and exclusion criteria—including a diagnostic telephone interview—and an explanation of the research terms (ie, study design, intervention length, and intervention rationale). Participants meeting the eligibility criteria and giving their informed consent will be allocated to the web-based intervention. A user account and password will be provided via email to each participant for individual use. Baseline assessment will be completed on the website and via a telephone interview before the intervention commences. Participants will be free to withdraw from the intervention or study at any time and without providing justification. In such cases, the research group will endeavor to contact them to ask for reasons and collect data regarding the feasibility of the internet-based intervention developed.

### Internet Attachment–Based Compassion Therapy

The intervention will consist of an internet-delivered version of ABCT [7]. ABCT is a compassion protocol based on the attachment theory and thus includes practices to raise awareness and/or address maladaptive aspects, where appropriate, of attachment styles developed with parents [6]. This process is taught as a form of both compassion and self-compassion to improve present-day interpersonal relationships and well-being in general [1]. ABCT consists of 8 group sessions, each of which has a 2-hour duration (1 session per week), including theory and both formal and informal compassion and self-compassion exercises and practices such as receiving and giving compassion to oneself, friends, unknown people, and people deemed to be problematic; identifying their own attachment style; and understanding how it influences their current interpersonal relationships, together with daily homework assignments that should take 15 to 20 min to complete [1,6].

iABCT will follow along the lines of the original model [6,7], and it will be adapted and developed to be totally self-applied over the internet via the website (Figure 1) [36], designed by the Laboratory of Psychology and Technology, Universitat Jaume I, and the University of Valencia. This platform allows several internet interventions including online assessments to be developed and hosted.

iABCT will consist of 8 sequential modules with the same structure: (1) module agenda; (2) theoretical contents of the module; (3) exercises and activities (including formal and informal practices) to put what is learned in the module into practice; (4) assessment of the knowledge acquired during the module; (5) tasks to be completed before advancing to the next module (homework assignments); and (6) summary of the module. The content will be presented through text, audios, videos, pictures, vignettes, and interactive exercises. Downloadable PDF files will be made available so that users can review them offline. Formal practices (guided meditations) will be delivered through audios with specific guides and instruction for each meditation. Furthermore, transcriptions of each guided meditation will be included as downloadable PDF files.

**Figure 1 figure1:**
[figure not shown]
A screenshot of the “Psicología y Tecnología” (Psychology and Technology) Web platform.

Table 1 presents the contents of each module. In comparison with the original ABCT, the adapted web-based version includes module 0, “Introduction to attachment-based compassion therapy,” to introduce to the participant the basics of the attachment-based compassion model and the program contents. Module 0 also includes tips about the use of formal and informal compassion (when/where/how much/how meditate) and on the importance of progressiveness in compassion training and of home practice between modules. Specific content has been added about “managing guilt” (formal meditation in module 4), “embarrassment” (theoretical component and formal practice in module 5), and “envy” (theoretical component and formal practice into module 7). Moreover, the term, “the figure of affect,” has been replaced by “basic affection” to make it easier to understand and so that participants will not confuse this with “the figure of secure attachment.” Other practices that have been eliminated are “showing forgiveness for the hurt caused by loved ones” (for people with grief experiences) and the “the illusion of labels” because they were not considered relevant for this protocol. Finally, module 8 on equanimity (“Beyond compassion: equanimity”) [6] has not been included in the web-based version because it was considered a different and advanced aspect of compassion.

The length of the interventions will depend on the pace of each participant, who will be advised to complete 1 module per week, taking the days between sessions to complete homework assignments. Each module has been optimized to allow it to be completed in approximately 1 hour. It is estimated that the web-based intervention can be completed in 8 weeks. However, each participant will be free to advance at his/her own pace with a maximum period of 10 weeks. Formal telephone support will not be systematically provided, but participants will be able to make contact for technical assistance (eg, web accessibility problems or forgotten passwords) if necessary.

**Table 1 table1:** Structure and contents of Internet Attachment–Based Compassion Therapy.

Module	Theoretical component	Formal practice	Informal practice
0: Introduction to attachment-based compassion therapy	What is compassion? Contexts of application Attachment-based compassion therapy: structure and rationale Meditation and compassion: formal and informal practice Tips about meditation practice: when/where/how much/how meditate The importance of progressiveness in compassion and homework	N/A^a^	3-min compassionate practice
1: Preparing ourselves for compassion. Kind attention	The workings of our brain The reality of suffering: primary and secondary suffering What is and is not compassion?	Compassionate breathing and compassionate body scan Compassionate in coping with difficulties	Self-compassion diary Savoring and giving thanks
2: Discovering our compassionate world	Going deeper into compassion and mindfulness terms Compassion and related terms Fear of compassion	Connecting with basic affection Developing a safe place The compassionate gesture Identifying the figure of secure attachment	The object that joins us to the world Diary of compassion practice What are we good at?
3: Developing our compassionate world	How compassion works The figure of secure attachment Efficacy of compassion Self-criticism	Developing the figure of secure attachment Developing the compassionate voice	Writing a letter to the figure of secure attachment
4: Understanding our relationship with compassion	The biological bases of compassion Attachment styles Guilt Importance of these styles in everyday life	Becoming aware of our attachment style Ability to receive affection: friend, indifferent person, and enemy Guilty repair practice	Letter to your parents Observing our attachment styles in daily life
5: Working on ourselves	The importance of the affection toward ourselves and others Embarrassment	Showing affection to friends and indifferent people Showing affection to ourselves Reconciliation with our parents Repairing embarrassment	The greatest display of affection (in general and from our parents) 3 positive aspects and 3 negative aspects of our parents
6: Understanding the importance of forgiveness	The concept of forgiveness Phases of forgiveness Utility of forgiveness Basic resistances to generate forgiveness Resources to generate forgiveness The recapitulation (optional)	Forgiving yourself Asking others for forgiveness Forgiving others and showing compassion to enemies	Interdependence Compassion in daily life
7: Consolidating the practice of compassion	Working in 3 periods (past, present, and future) Envy Usefulness of being our attachment figure Difficult relationships How to keep up the practice of compassion for a lifetime	Working with envy Becoming our own attachment figure Handling difficult relationships	Not taking anything personally Our values and their relationship with compassion What would our lives be like if we started over?

^a^N/A: not applicable.

